##### Productivity losses (PRODISQ)

Production losses will be measured using the PROductivity losses and DISability Questionnaire (PRODISQ), a module-based questionnaire. This questionnaire will be used only for those with a paid job. Three modules will be used for this study to gather data on absenteeism and presenteeism. Production costs will be calculated by using the friction cost method [27,28].

##### Productivity losses (PRODISQ) and School absenteeism

For the young people who go to school, we adjusted the same three modules from the PRODISQ as we did to measure absentieesm and presenteeism among the working young persons.

#### III) Process evaluation

##### Qualitative Interviews

Interviews will be conducted with the caregivers of the mental health services who provide the online Kopstoring program. We will ask them questions about offering the program as described in the protocol and about the process of enrolment. In addition to conducting these qualitative interviews with caregivers, we will send a short online questionnaire to the program respondents.

##### Credibility/Expectations Questionnaire (CEQ)

The credibility and expectations questionnaire, a 6-item list, is used to determine what the respondents expect from the online program and how many credits they give the intervention.

Credibility and Expectations will be measured by the Credibility/Expectations Questionnaire (CEQ) which consists of 6 items using a 9- or sometimes 10-point Likert scale. This instrument is meant to measure the expectations and credibility a person has about the received intervention [29]. The questionnaire can be used at baseline and during follow-up to compute the different scores in expectation and credits one gives to a particular therapy. In their article Borkovec et al show that the instrument has proven to be valid and that the psychometric properties are of good quality[30]. It will take around five minutes to complete the 6 items of this instrument.

### Analyses

Data will be analysed according to the intention-to-treat principle, which means including data from all participants irregardless of whether they received the intervention or not. Missing data on the item level will be handled using SPSS missing values analysis. Completely missing measurements will be handled using multiple imputation. A baseline analysis will be performed to examine the comparability of groups at baseline for both costs and outcomes. Differences in baseline will be controlled using applied methods to correct these differences [31]. Losses to follow-up will be described.

The analysis consists of comparing the assessments and scores of the respondents on the questionnaires. Clinical outcomes after the intervention (8 weeks), at three months, six months and twelve months will be compared between groups and within groups, which means we want to compare the effect of the intervention in respondents in the intervention and control groups and assess the additional effects before and after receiving the intervention.

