**Methods/Design:**

We designed a randomized controlled trial to examine the (cost-) effectiveness of the Kopstoring intervention. Kopstoring is an online intervention for COPMI-children to strengthen their coping skills and prevent behavioral and psychological problems. We will compare the Kopstoring intervention with (waiting list) care as usual. This trial will be conducted entirely over the internet. An economic evaluation, from a societal perspective will be conducted, to examine the trial's cost-effectiveness. Power calculations show that 214 participants are needed, aged 16-25. Possible participants will be recruited via media announcements and banners on the internet. After screening and completing informed consent procedures, participants will be randomized. The main outcome is internalizing and externalizing symptoms as measured by the Youth Self Report. For the economic evaluation, healthcare costs and costs outside the healthcare sector will be measured at the same time as the clinical measures, at baseline, 3, 6 and 9 months. An extended measure for the intervention group will be provided at 12 months, to examine the long-term effects. In addition, a process evaluation will be conducted.

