### Design

This study will consist of an effectiveness study, an economic evaluation study and a process evaluation.

The basis of the effectiveness study will be a pragmatic randomized controlled trial (RCT), in which the Kopstoring program will be compared with a waiting list control condition which reflects care as usual (CAU). The interventions last 8 consecutive weeks with a ninth meeting after a month. Figure 1 presents the flow chart for the study. Cost and outcome measures will be taken at baseline and at 3 months and 6 months after baseline in both conditions. An extended follow-up at 12 months will be conducted in the intervention arm of the trial, to monitor the long-term costs and effects of the intervention.

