### Utilities

Utilities will be derived from the EQ-5D using the following steps. The 5 dimensions will be summarized into a health state. Utility values will be calculated for these health states, using preferences elicited from a general population, the so-called algorithms. One algorithm has been established using a general population from the UK, the Dolan tariff [24]. For the sensitivity analysis the Dutch algorithm will be used [25]. The utility values derived will be used to compute Quality Adjusted Life Years (QALYs). A QALY combines survival and utilities. The utilities at the three time points will be used to compute the Quality Adjusted Life Years gained (QALY) using of the area under the curve method.

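### The Analyses section promises a between-group comparison at twelve months, but only the intervention arm is assessed then, and the abstract, Design and Analyses sections give different assessment schedules

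*Protocol article*

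**What the plan says.** Three places in the protocol article set out when participants are assessed or compared.

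- **Abstract, Methods/Design.** Costs "will be measured at the same time as the clinical measures, at baseline, 3, 6 and 9 months". It then adds: "An extended measure for the intervention group will be provided at 12 months, to examine the long-term effects".
- **Design.** "Cost and outcome measures will be taken at baseline and at 3 months and 6 months after baseline in both conditions". For the later visit: "An extended follow-up at 12 months will be conducted in the intervention arm of the trial".
- **Analyses.** "Clinical outcomes after the intervention (8 weeks), at three months, six months and twelve months will be compared between groups and within groups". The same section says: "Completely missing measurements will be handled using multiple imputation".

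Three other sections bear on the horizon. Design ties the primary economic outcome to 6 months of follow-up. Utilities computes QALYs from three time points. The economic part of the analysis section takes the effect terms of the cost-effectiveness ratio at 6 months but defines the cost term of each arm as a yearly total.

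**The concern.** A between-group comparison needs outcome data from both groups at the same time. At twelve months the plan names such a comparison while its own design collects data from one group. An analyst who follows the Analyses section literally either cannot do what it says or must find a substitute for the missing arm.

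The abstract gives long-term effects as the purpose of the 12-month measurement. Change within the intervention arm over a year mixes any effect of the course with natural course, regression to the mean and selective drop-out. Randomisation protects against none of these once the control arm is no longer observed.

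The disagreement over 9 months matters for a related reason. It leaves the time of the last randomised comparison stated in two ways, and with it the period over which costs can be observed in both arms.

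**Working it through.** No power or precision figure decides this point, so the check is to set the schedules side by side.

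| Time point | Abstract | Design | Analyses (between and within groups) |
|---|---|---|---|
| Baseline | yes | both arms | not listed |
| 8 weeks | no | no | named as post-intervention |
| 3 months | yes | both arms | yes |
| 6 months | yes | both arms | yes |
| 9 months | yes | no | no |
| 12 months | intervention only | intervention only | yes |

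**Step 1: between-group comparisons against visits in both arms.** Analyses names {8 weeks, 3, 6, 12 months}. Design assesses both arms at {0, 3, 6 months}. Removing the second set from the first leaves {8 weeks, 12 months}.

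**Step 2: the same against the intervention arm alone.** Design assesses that arm at {0, 3, 6, 12 months}. Removing these from the Analyses list leaves {8 weeks}. A within-arm comparison at 12 months is therefore feasible in the intervention arm; a between-arm one is not.

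**Step 3: abstract against Design.** {0, 3, 6, 9} less {0, 3, 6} leaves {9 months}. On 12 months the two agree: intervention arm only. So no version of the schedule gives controls a 12-month assessment.

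**Step 4: size of the gap.** The enrolment target is 214. With equal allocation, as the equal requirement of 78 per condition implies, 214 / 2 = 107 controls, and 0 of 107 are due for assessment at 12 months. (The article's own division, 156 / (1 − 0.28), gives 216.7 rather than 214; the small difference has no bearing here.)

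**Step 5: which schedule the economic sections fit.**

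- QALYs from three time points fit 0, 3 and 6 months. The abstract's both-arm list would give four.
- Effect terms at 6 months fit the same schedule.
- Yearly cost terms do not. After baseline, control costs are followed for 6 of 12 months under Design, or 9 of 12 under the abstract. Neither reaches a year. The intervention arm could supply 12-month costs, since Design says its extended follow-up covers costs, but there is no matching control figure.

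**The case against.** The strongest reply is that the Analyses sentence is compressed: it lists all time points once for two kinds of comparison, and twelve months was meant for the within-group kind only. The abstract and Design both state the restriction to the intervention arm openly, and the Analyses section speaks of effects before and after the intervention, which can be examined in one arm. That may well be the intent. But the sentence applies both comparisons to every time point without qualification, so it still needs correcting.

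Several stronger readings are tempting, and the reply defeats them:

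- **Imputed controls.** A reader might infer that multiple imputation will fill in all control values at 12 months. The article does not say so. The rule on completely missing measurements is most naturally read as covering scheduled visits that were missed. If it were stretched to 12 months, no observed control value would inform the arm difference, which is reason enough to exclude it in words.
- **A before-after result presented as randomised.** Nothing in the article states that intention.
- **No data in either arm at 8 weeks.** The 8 weeks directly follow the mention of the intervention and match the length of the course, so they may be a gloss. The Process evaluation section does have credibility and expectancy measured after the course, though that is not a clinical outcome. Listing the point separately from three months favours a distinct visit but does not settle it. The flow chart, which is not available here, might help.

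As for 9 months, it is probably a slip in the abstract, since the QALY and effect definitions fit 0, 3 and 6 months. It remains a contradiction in the text. The flow chart could show which version was meant, but it could not make the statements agree.

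**Conclusion.** The concern holds for twelve months. The named between-group comparison has no control data by design, on the agreement of the abstract and Design, and only an uncontrolled description of the intervention arm is possible. Under the Design schedule the randomised comparison ends at 6 months, half the twelve months named in Analyses. If the abstract's 9-month visit proved real in both arms, it would end at 9 months; the 12-month conclusion would not change.

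The 9-month entry is a plain contradiction between abstract and Design. The 8-week point is a query, not an established error.

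It would be wrong to conclude that the economic evaluation as a whole fits the 6-month schedule. The QALY and the effect terms do; the yearly cost terms do not.

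The 3- and 6-month comparisons and the sample size are untouched. The only assumption is equal allocation, and it affects only the count of 107.

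**What to change.** 1. State one assessment schedule per arm and bring the abstract, Design and Analyses into line with it, including whether a 9-month measurement exists and in which arms.
2. Clarify whether the 8 weeks in Analyses name a clinical assessment or only the length of the course. If it is an assessment, add it to the schedule for the arms concerned.
3. Limit between-arm comparisons to time points assessed in both arms: 3 and 6 months under Design as it stands. Remove twelve months from the between-group comparison.
4. Describe the 12-month intervention-arm results as descriptive and uncontrolled.
5. Say that multiple imputation applies to scheduled visits only, so that it creates no 12-month control values.
6. Reconcile the yearly cost terms of the cost-effectiveness ratio with the 6-month horizon observed in both arms, so that costs and effects cover a stated and comparable period.

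The cost is redrafting; no added visit or larger sample is needed. The downside is that the long-term result becomes descriptive, which is all that a single-arm 12-month assessment can support.

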#### II) Economic evaluation study

The economic analysis will also be performed according to the intention-to-treat principle. Handling of missing data will be similar to the effectiveness study. A baseline analysis for the economic evaluation will also be performed to examine the comparability of groups at baseline for both costs and outcomes. If necessary methods will be applied to control for differences in baseline [31]. Despite the usual skewness in the distribution of costs, the arithmetic means are generally considered to be the most appropriate measures to describe cost data [32]. Therefore arithmetic means (and standard deviations) will be presented. Non-parametric bootstrapping will be used to test for statistical differences in costs between the intervention and control group. Non-parametric bootstrapping is a method based on random sampling with replacement based on the participants' individual data [33]. The bootstrap replications will be used to calculate 95% confidence intervals around the costs (95% CI), based on the 2.5th and 97.5th percentiles.

The incremental cost-effectiveness ratio (ICER) will be determined on the basis of incremental costs and the effects of the Kopstoring program in comparison with care as usual. The cost-effectiveness ratio will be stated in terms of costs per unit of outcome; the cost-utility ratio will focus on the incremental cost per QALY gained. The ICER will be calculated as follows. ICER = (Ci - Cc)/(Ei - Ec), where Ci is the annual total cost of the Kopstoring group, Cc is the annual total cost of the care as usual group, Ei is the effects at the 6-month follow-up for the Kopstoring group and Ec is the effect at the 6-month follow-up for the care as usual group. The robustness of the ICER will be checked by non-parametric bootstrapping. Bootstrap simulations will also be conducted in order to quantify the uncertainty around the ICER, yielding information about the joint distribution of cost and effect differences. The bootstrapped cost-effectiveness ratios will be plotted subsequently in a cost effectiveness plane, in which the vertical line reflects the difference in costs and the horizontal line reflects the difference in effectiveness. The choice of treatment depends on the maximum amount of money that society is prepared to pay for a gain in effectiveness. Therefore, the bootstrapped ICERs will also be depicted in a cost-effectiveness acceptability curve, showing the probability that Kopstoring is cost-effective using a range of ceiling ratios. To demonstrate the robustness of our base-case findings a multi-way sensitivity analyses will be performed in which assumptions in the base case analysis will be recalculated to assess whether they have influenced the incremental cost-effectiveness ratio (ICER), for example by varying unit costs and volumes between minimum and maximum [33]. The bootstrap replications will be used to calculate 95% confidence intervals around the median costs, while the 95% CI will be based on the 2.5th and 97.5th percentiles.

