### Target population

The target group is defined as young people aged between 16 and 25 years who have at least one parent suffering from a psychiatric disorder, multiple psychological disorders or an addiction problem. For inclusion in our study, young people have no internalizing and externalising problems. This will be defined using the Youth Self report List (YSR); the cutoff scores for girls will be a score of 21 and for boys a score of 16. If the young person has a score above the cutoff score, they will be referred for treatment or other services. In addition, the young person has to be sufficiently fluent in the Dutch language, have access to the internet and be able to use a chat box - to participate actively and be able to listen to other participants. For young people aged 16-17 informed consent from the parent is also required. For those aged 18 and over, informed consent of the adolescent is sufficient. Those who are younger than 16 years or older than 25 years are excluded from our study.

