### Intervention

The Kopstoring program consists of 8 consecutive online weekly chat group meetings and a ninth evaluation meeting in a chat box at the website http://www.kopstoring.nl. The aim of the intervention is to strengthen protective factors, such as self-management skills and psychological well-being, and prevent the development of psychological disorders. The experts (prevention workers and psychologists from mental health care institutions) involved in the delivery of the intervention are specialized in the field of COPMI-problems and in the prevention of mental health problems in young people. The intervention is protocol-driven and well-structured. There are 8 themes, so each week there is a new theme. The themes are; getting acquainted with the home situation, roles in families, thoughts and feelings, questions about addiction and mental problems, different styles of behaviour, social networks, leading your own life in relation to social networks and what is coming up in the future. The participants are required to carry out homework assignments before entering the chat box (chat room) meeting [18]. The Kopstoring program is part of an informative website which also provides an e-mail service and chat options, alongside the Kopstoring program.

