### Care as usual in the Netherlands

The control condition in this trial is a waiting list with unrestricted access to care as usual. Usual care in the Netherlands is a mix of several services. In this study, care as usual is not standardized and there are no protocols. Young people can request a lot of services: for example, a general practitioner, a psychologist, or mental health or institutional services such as counselling sessions.

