### Sample Size calculation

The sample size calculation is based on the ability to detect a medium size or larger clinical effect. This corresponds to a standardized mean difference (Cohen's d) of d > 0.45 [19]. We will test the hypotheses at a conventional power of (1 - beta) = 0.80 and alpha = 0.05, 2-tailed (cf. Friedman et al., 1996). For this n = 78 is required per condition, therefore a total of 156 participants. Finally we want to compensate for possible drop-out during the trial. The drop-out rate from the pilot study was 28% [9]. We therefore need to enrol 156/(1-0.28) = 214 participants during the trial.

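### Kopstoring is delivered in chat groups, but the sample size makes no allowance for within-group correlation and the cost bootstrap is described as resampling individuals

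*Protocol article*

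**What the plan says.** Under Intervention, the protocol article states: "The Kopstoring program consists of 8 consecutive online weekly chat group meetings and a ninth evaluation meeting in a chat box". Under Target population, participants must be able "to participate actively and be able to listen to other participants", so exchange between members is part of the course. Under Care as usual in the Netherlands, the comparator is described thus: "The control condition in this trial is a waiting list with unrestricted access to care as usual". No grouping of controls is mentioned.

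The Sample Size calculation section gives the effect size ("This corresponds to a standardized mean difference (Cohen's d) of d > 0.45") and the error rates ("conventional power of (1 - beta) = 0.80 and alpha = 0.05, 2-tailed"), and concludes: "For this n = 78 is required per condition, therefore a total of 156 participants". The only inflation is for 28% drop-out.

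Under Analyses, II) Economic evaluation study, cost differences are tested by bootstrap, with percentile 95% intervals. The technique is described as follows: "Non-parametric bootstrapping is a method based on random sampling with replacement based on the participants' individual data". The same section uses bootstrapping again for the incremental cost-effectiveness ratio (ICER), the cost-effectiveness plane and the acceptability curve. Neither the sample size section nor the Analyses section mentions chat group as a source of correlation.

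**The concern.** This is a partially nested design: participants are clustered in one arm and not in the other. Members of a chat group work through the same themes together for eight weeks and can influence each other, so their outcomes, and possibly their use of care, may be more alike than those of participants from different groups. The mean of the Kopstoring arm then carries a between-group variance component that a formula for independent observations leaves out. Resampling individuals breaks up the groups and leaves it out as well.

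Cost-effectiveness is the main research question, and the Discussion says that a favourable result would lead to the aim of implementing the programme as standard care. An acceptability curve that looks more certain than it should would bear directly on that decision.

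**Working it through.** **Inputs from the article:** d = 0.45 (SD = 1), two-sided alpha 0.05, power 0.80, 78 evaluable participants per arm, drop-out 28%.

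**Assumed, because not given:** m = 4 to 10 evaluable members per chat group, and ICC = 0.01 to 0.10. Total variance is taken as equal in the two arms, and the normal approximation is used.

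**Step 1: reproduce the plan's figure.** For independent observations, n per arm = 2 × (1.960 + 0.842)² / 0.45² = 77.5, rounded up to 78. Power at 78 is Φ(0.45/√(2/78) − 1.96) = Φ(2.810 − 1.960) = 0.802. The stated number contains no design effect and has almost no slack.

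**Step 2: add clustering in the Kopstoring arm only.**

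- Design effect in that arm: DE = 1 + (m − 1) × ICC
- Variance inflation of the difference: (DE + 1)/2
- Ratio of correct to naive standard error: √[(DE + 1)/2]
- Power: Φ(0.45/√[(2/78) × (DE + 1)/2] − 1.96)
- Actual coverage of a naive 95% interval: 2Φ(1.96/SE ratio) − 1

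For m = 8 and ICC = 0.05, DE = 1 + 7 × 0.05 = 1.35, the inflation is 2.35/2 = 1.175, and the SE ratio is √1.175 = 1.084. Power is Φ(0.45/0.1736 − 1.96) = 0.736.

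| m | ICC | DE | Inflation | SE ratio | Power at 78 per arm | Coverage of naive 95% interval |
|---|---|---|---|---|---|---|
| 4 | 0.01 | 1.03 | 1.015 | 1.007 | 0.797 | 94.8% |
| 6 | 0.02 | 1.10 | 1.050 | 1.025 | 0.783 | 94.4% |
| 6 | 0.05 | 1.25 | 1.125 | 1.061 | 0.755 | 93.5% |
| 8 | 0.05 | 1.35 | 1.175 | 1.084 | 0.736 | 92.9% |
| 8 | 0.10 | 1.70 | 1.350 | 1.162 | 0.677 | 90.8% |
| 10 | 0.10 | 1.90 | 1.450 | 1.204 | 0.646 | 89.6% |

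**Step 3: sensitivity to what m means.** The 78 are participants left after drop-out, so m must be the evaluable group size. If eight is the size at the start and losses are spread evenly, 8 × 0.72 = 5.76 remain. At ICC 0.05, DE = 1 + 4.76 × 0.05 = 1.238 and power is 0.757 rather than 0.736. Starting from ten at ICC 0.10, 7.2 remain, DE = 1.62 and power is 0.690 rather than 0.646.

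The power column concerns the clinical effect size. The SE ratio and coverage columns do not depend on d, so they indicate what happens to cost intervals if costs have an ICC in this range. They are approximate there, because costs are skewed and the two arms may differ in variance.

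**The case against.** The strongest objection is that the size rests wholly on two assumed inputs. With small groups and an ICC of 0.01 or 0.02, power stays within about two points of 0.80, and nothing in the article supports any particular ICC, least of all for costs. The intention-to-treat analysis also includes Kopstoring participants who never joined a group, and their outcomes are not correlated through one. All of this stands. It is why the conclusion is conditional and given as a range.

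Second, the sentence on bootstrapping is a general description of the technique and does not expressly rule out resampling by group. That is fair, but it names the individual's data as the basis, no other unit appears anywhere, and individual resampling is the natural reading.

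Third, a reader might infer that the type I error of the primary clinical comparison exceeds 5%. The article does not support this. The Analyses section names no test or model for the clinical outcomes, so no independence assumption is fixed there, and the model may properly be left to an analysis plan. The interval problem attaches to the bootstrap for costs and the ICER.

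A reader might also assume that each group shares one course leader, or that the course system already holds a group identifier. The article says only that experts deliver the course and that a database system exists. Neither assumption is needed for the point.

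**Conclusion.** The point holds in conditional form. Delivery in groups, a sample size without a design effect, and a bootstrap described at the individual level all stand in the article, so this is more than a detail left to an analysis plan. For any positive within-group correlation, with equal total variances, the stated power is overstated and the bootstrap intervals are too narrow.

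Under the assumed 4 to 10 evaluable members and ICC of 0.01 to 0.10, power is about 0.80 to 0.65 and the correct standard error is 1.01 to 1.20 times the naive one. For groups of 6 to 8 at ICC 0.05, power is about 0.74 to 0.76 and the ratio is 1.06 to 1.08. The loss may be negligible. That 80% power is certainly missed by a material amount cannot be concluded from the article. This is a correctable overstatement of precision and does not invalidate the design.

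**What to change.** - Record each Kopstoring participant's chat group in the trial data.
- In the bootstrap for costs, the ICER and the acceptability curve, resample whole chat groups in the Kopstoring arm and individuals in the control arm. Treat Kopstoring participants who never joined a group as single-member clusters.
- For the clinical outcomes, use a model with a random chat-group effect in the Kopstoring arm only, so that the analysis matches the design. This adds to the article and does not correct a stated model.
- Restate the power in the Sample Size calculation section as a partially nested design, with an assumed group size and a range of ICCs. The trial need not be enlarged.

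The cost is one recorded variable and some analysis wording. Randomization and the questionnaires do not change. The downside is slightly wider intervals and a less favourable stated power. With 78 evaluable participants in the arm there would be only about 8 to 20 groups (78/10 = 7.8; 78/4 = 19.5), so resampling groups is itself approximate, and the number of groups should be reported with the results.

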**Figure 1 F1:**
[figure not shown]
**Flow chart study design**.

In the economic evaluation we will compare incremental costs and incremental outcomes of the Kopstoring intervention in relation to care as usual. This economic evaluation will involve both a cost-effectiveness analysis (CEA) and a cost-utility analysis (CUA). The primary outcome measure for the economic evaluation will be the prevention of the development of symptoms over the 6 months of follow-up. Within the cost-utility analysis, outcomes will be measured by means of the standard Dutch version of the EuroQol. In the CEA, the incremental cost-effectiveness ratio (ICER) will be expressed as the incremental costs per point improvement on the Youth Self Report Questionnaire. The primary outcomes measured for the cost-utility analysis will be QALYs, based on the EuroQol utility scores [15,16]. In the CUA, the ICER will be expressed as the incremental cost per QALY. This economic evaluation will take a societal perspective, including all relevant costs and outcomes.

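### The ICER formula sets annual costs against 6-month effects, and the control arm has no scheduled 12-month measurement to supply an annual cost

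*Protocol article*

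**What the plan says.** The formula is in the Protocol article, Analyses, II) Economic evaluation study: ICER = (Ci - Cc)/(Ei - Ec). The costs are defined by "where Ci is the annual total cost of the Kopstoring group, Cc is the annual total cost of the care as usual group". The intervention-arm effect is defined by "Ei is the effects at the 6-month follow-up for the Kopstoring group"; the control-arm effect, Ec, is defined in the same way, also at 6 months. The formula is stated once, directly after the sentence that introduces both the cost per unit of outcome and the cost per QALY, so it governs both ratios.

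The other statements on timing are:

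- Design: "Cost and outcome measures will be taken at baseline and at 3 months and 6 months after baseline in both conditions". The same section adds: "An extended follow-up at 12 months will be conducted in the intervention arm of the trial".
- Economic evaluation paragraph after Figure 1: the primary economic outcome is the "prevention of the development of symptoms over the 6 months of follow-up".
- Utilities: "The utilities at the three time points will be used to compute the Quality Adjusted Life Years gained", by the area under the curve.
- Abstract, Methods/Design: costs are measured "at the same time as the clinical measures, at baseline, 3, 6 and 9 months". The 12-month measure is again for the intervention group only.
- Analyses, opening section: clinical outcomes are to be compared between and within groups at time points that include twelve months.

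**The concern.** An incremental ratio can be interpreted only if costs and effects cover the same period. Here the numerator covers twelve months and the denominator stops at six. For the cost-utility ratio the mismatch is direct, because QALYs accumulate over time and are accumulated here over half a year only. For the cost per YSR point, the numerator contains costs incurred after the effect was measured, which cannot have produced it.

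The second problem is the source of the control arm's annual cost. Part of it has no scheduled measurement, whereas the intervention arm is assessed at 12 months. Without a stated rule, the two terms of the numerator would be obtained differently. If waiting-list participants were given the course within the year, their annual cost would also contain the course; the article does not say whether or when that happens.

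The main research question is societal cost-effectiveness. The two ratios, their bootstrap intervals, the cost-effectiveness plane and the acceptability curve all use this cost difference.

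**Working it through.** The article states no ICER, cost difference or QALY difference, so there is no figure of its own to reproduce. The check has two parts: a comparison of the time windows, which rests on the documents alone, and an illustration of size, which rests on assumptions.

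**Time windows**

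| Quantity | Window | Source |
|---|---|---|
| Ci, Cc | 12 months | ICER formula |
| Ei, Ec | 6 months | ICER formula |
| Primary economic outcome | 6 months | Paragraph after Figure 1 |
| QALYs, three time points | 0, 3, 6 months, if the Design schedule applies | Utilities with Design |
| Cost measurement, both arms | to 6 months, or to 9 months | Design, or abstract |
| 12-month measurement | intervention arm only | Design and abstract |

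Months of control cost without scheduled data: 12 - 6 = 6 under the Design section, or 12 - 9 = 3 under the abstract.

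**Size, first illustration (all inputs assumed)**

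Let P be the one-off programme cost, c the other costs per half-year in the control arm, and s the relative saving in those costs, constant over the year. Then:

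- 6-month cost difference = P - s·c
- annual cost difference = P - 2·s·c

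The QALY gain is taken as 0.01 over 6 months.

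| P | c | s | 6-month difference | Annual difference | Per QALY, 6-month costs | Per QALY, annual costs |
|---|---|---|---|---|---|---|
| 400 | 1,500 | 10% saving | 400 - 150 = 250 | 400 - 300 = 100 | 25,000 | 10,000 |
| 400 | 1,500 | 10% increase | 400 + 150 = 550 | 400 + 300 = 700 | 55,000 | 70,000 |
| 400 | 3,000 | 10% saving | 400 - 300 = 100 | 400 - 600 = -200 | 10,000 | negative: costs lower, effect better |

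**Size, general form (inputs assumed)**

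Let the cost difference to month T be P + r·T, with r the monthly difference in other costs. With the 6-month effect held fixed, the written formula equals the matched 6-month ratio multiplied by (P + 12r)/(P + 6r).

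| P | r per month | To 6 months | To 12 months | Factor |
|---|---|---|---|---|
| 300 | 0 | 300 | 300 | 1.0 |
| 0 | +50 | 300 | 600 | 2.0 |
| 300 | +50 | 600 | 900 | 1.5 |
| 300 | -20 | 180 | 60 | 0.33 |
| 300 | -40 | 60 | -180 | -3.0 |
| 300 | -60 | -60 | -420 | 7.0 |

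**The denominator, seen from the other side**

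Over 0, 3 and 6 months no participant can accrue more than 0.5 QALY. Assume a utility gain of 0.05, reached linearly at 3 months and then held.

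- 6-month gain: 0.25 × (0 + 0.05)/2 + 0.25 × 0.05 = 0.00625 + 0.0125 = 0.01875 QALY.
- 12-month gain: 0.01875 + 0.5 × 0.05 = 0.04375 QALY.
- Annual costs divided by the 6-month gain give 0.04375/0.01875 = 2.33 times the matched 12-month cost per QALY.

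**The case against.** The best counter-argument is that *annual* is a drafting slip. It is used for costs in this sense only in the formula, while the economic outcome is elsewhere set over 6 months, so the analysis as run might well use 6-month costs. That is plausible. It supports the proposed correction, but it does not make the written rule right.

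*Annual* could also mean 6-month costs scaled to a year, which would at least treat the arms alike. No such step is described. It would leave the 6-month denominator unmatched, and it would scale up a one-off 8-week course that should not be scaled by time.

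The opening of Analyses speaks of comparing groups at twelve months, which sits badly with a flat statement that only the intervention arm is followed that long. That sentence concerns clinical outcomes. Neither the Design section nor the abstract schedules a 12-month control assessment, and the effects in the formula would still be at 6 months. It does show that the schedule is inconsistent and that correcting the formula alone is not enough.

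Multiple imputation does not fill the gap: with no control participant scheduled at 12 months, no observed control costs would inform it. The planned sensitivity analysis gives unit costs and volumes as its example, not the time horizon.

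Three limits stand. A 6-month YSR score is a state at one time, so the mismatch is less strict for that ratio than for QALYs. The possible provision of the course to controls within the year is conditional and carries no weight here. The size of the distortion rests wholly on assumed inputs.

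**Conclusion.** The concern holds. As written, the formula combines 12 months of cost with 6 months of effect, and 6 months (Design) or 3 months (abstract) of the control arm's annual cost have no scheduled data. This follows from the document's own definitions and needs no assumption.

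The size and direction of the distortion cannot be derived from the article. Under the assumed scenarios the written formula gives between -3.0 and 7.0 times the matched 6-month ratio. It doubles the ratio when the arms differ only by a constant monthly cost, and leaves it unchanged when they differ only by a one-off programme cost. A change of sign is possible when later savings offset the programme cost; it is not an expected result. The clinical effect analysis is not touched. Because the defect lies in the rule that produces the answer to the main research question, it must be corrected before the economic analysis is run.

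**What to change.** In Analyses, II) Economic evaluation study, define Ci and Cc as the mean total cost per participant from baseline to the 6-month follow-up in the Kopstoring and care-as-usual groups. Keep Ei and Ec as the YSR effect at 6 months for the cost-effectiveness ratio and as the QALY area under the curve from baseline to 6 months for the cost-utility ratio. Use the same window for the bootstrap, the cost-effectiveness plane and the acceptability curve. Report 12-month intervention-arm costs descriptively, outside the ICER.

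At the same time:

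- name the three time points in Utilities as baseline, 3 and 6 months;
- reconcile the 9-month measurement in the abstract with the Design section;
- reconcile the twelve-month between-group comparison in Analyses with a 12-month follow-up held in one arm only.

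The core change is one sentence, with short consistency edits elsewhere. No new data are needed, provided that the resource-use questionnaire, which the article says is still to be developed, has recall periods that together cover baseline to 6 months in both arms.
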